# The ARUTIS Study (Anglia Ruskin University Trial of the Intuitive System): a single-centre, double-masked randomised controlled crossover trial of precision tinted lenses for visual stress: study protocol for a randomised controlled trial

**DOI:** 10.1186/s13063-025-09305-8

**Published:** 2025-12-16

**Keywords:** Visual stress, Intuitive system, Intuitive colorimeter, Colorimetry, Precision tinted lenses, Wilkins rate of reading test, Symptoms

## Abstract

**Background:**

Visual stress (VS), a condition affecting approximately 20% of children with reading difficulties that is alleviated with individually prescribed coloured filters, remains controversial. The purpose of the Anglia Ruskin University Trial of the Intuitive System (ARUTIS) is to investigate the effect of wearing precision tinted lenses (PTL) prescribed by the Intuitive System (IS) in children with VS using a double-masked crossover design.

**Methods:**

A total of 120 participants aged 9–18 years meeting diagnostic criteria for VS will be recruited from the Anglia Ruskin University Eye Clinic. A widely used instrument, the Intuitive Colorimeter, will be used to select, for each participant, the chromaticity of precision tinted lenses (PTL) that they claim optimally alleviates their symptoms and a similar control colour will also be determined. Participants will be randomised into group 1, receiving spectacles with intervention A (optimal tint) followed by B (sub-optimal tint), or group 2, receiving the two interventions in the order BA. The first intervention will be used for 1 month, followed by a 1-month washout period, the second intervention for 1 month, and then a head-to-head comparison in the clinic with participants invited to keep their preferred pair of spectacles. The primary outcome measurement is symptoms (measured by symptom diaries and symptom questionnaires); the secondary outcome measure is observed school performance (measured by academic behaviour surveys); and the tertiary outcome measure will be reading speed (measured by the WRRT).

**Discussion:**

Reviews on VS have reached contradictory conclusions, noting the need for stronger evidence. This trial will be the first in children to use modern diagnostic criteria and will strengthen the evidence base concerning the widespread but still controversial use of coloured filters for children with VS who struggle to read.

**Trial registration:**

Prospectively registered to clinicaltrials.gov on 17th October 2023 with a unique protocol ID of ETH2223-7100.

**Supplementary Information:**

The online version contains supplementary material available at 10.1186/s13063-025-09305-8.

## Background

Visual stress (VS) is a condition characterised by symptoms of eye strain, headache, and visual perceptual distortions when reading [1–7] that are reported to be alleviated by individually selected coloured filters [5, 8–15]. VS is controversial [8, 16, 17]. Much of the controversy may be explained by studies and reviews conflating VS with dyslexia. Evidence indicates that these are separate conditions that sometimes co-occur, with VS affecting approximately 20% of people with dyslexia [13]. There is literature that claims the treatment of VS with coloured filters is attributable to placebo effects [8, 16, 17] but also publications [1, 3, 5, 9, 13, 18, 19] asserting that coloured filters reduce symptoms of asthenopia and visual perceptual distortions that occur in people with VS. There is a consensus that further clinical trials are needed to evaluate the effect of colour on the symptoms of VS.

A neurological theory for VS was originally proposed in 1984 on the basis that the visual stimuli that evoke discomfort are generally those that also induce seizures in patients with photosensitive epilepsy [6, 20]. Striped patterns are particularly problematic, and text forms a striped pattern that can trigger symptoms [6]. A neural mechanism for VS has found support in studies showing that the visual stimuli that induce discomfort also induce a large haemodynamic response, both in absolute terms and relative to the response to comfortable stimuli [21]. Individuals who are particularly susceptible to discomfort exhibit an abnormally large haemodynamic response [22, 23].

This work led to the cortical hyperexcitability hypothesis for the aetiology of VS. If the cortex is hyperexcitable, it is likely that the hyperexcitability is not diffuse but patchy, as it is in photosensitive epilepsy, where small areas of the visual cortex that respond, for example, to certain orientations of lines can trigger seizures [7]. It has been argued that precision tinted lenses (PTLs) rearrange cortical activity in such a way as to avoid strong excitation in hyperexcitable regions [24]. The avoidance of strong excitation in hyperexcitable regions prevents the spread of excitation and, in doing so, prevents the inappropriate firing of visual neurons that gives rise to illusions and distortions [24].

In 1994, Wilkins et al. [5] carried out a randomised crossover trial (RCT) that aimed to detect whether PTLs relieve symptoms of VS when reading. For participants who completed this trial, symptomatic days were significantly less frequent with the experimental PTLs compared to the control PTLs.

However, this study has received criticism [20], as there was significant attrition, which could have led to an overestimation of the benefits from PTLs. Conversely, the selection criteria were broad, which may have underestimated the benefit of the PTLs by including participants who did not have VS. During the study, reading was assessed with The Neale Analysis of Reading Ability [20]. This test is used to detect reading age and comprehension levels in school-aged children and uses large text and widely spaced lines which means that the test is unlikely to detect a benefit from optometric interventions.

Subsequently, the Wilkins Rate of Reading Test (WRRT) [25] was developed with features that make it well-suited to investigating the effect of optometric interventions. This test has been widely used in research on VS and other optometric interventions [25, 26], but was not available at the time of the 1994 study [5, 25].

Two systematic reviews relating to VS were published in 2016 and reached different conclusions. A review by Evans and Allen [13] concluded that VS affects about 20% of people with reading difficulties and can be alleviated with coloured filters. The other review, by Griffiths et al. [20] concluded that the “use of coloured lenses or overlays to ameliorate reading difficulties cannot be endorsed” and argued that reported beneficial effects may be attributable to the placebo effect [6]. Both reviews agreed that this is a difficult area to research, and more trials are needed. Both note the limitations of the research and accept that there is not a high level of evidence. The different conclusions of the two reviews may be explained, at least in part, by the fact that the reviews asked different questions. Griffiths et al. ask whether coloured filters improve reading and therefore concentrate on reading skills. An earlier review concluded that coloured filters improve symptoms in VS but found that there is insufficient evidence to state whether they improve reading in those with reading difficulties [17]; therefore, the conclusion of Griffiths et al. was not unheralded. The Evans and Allen review concentrated on symptoms and, unlike Griffiths et al., focused on studies that used the scientifically designed Wilkins “Intuitive System” (IS) and, most importantly, studies of people with the target condition of VS [13]. The Griffiths et al. review included studies of populations with reading difficulties such as dyslexia, which would have been markedly underpowered because most people with dyslexia do not have visual stress [13].

The IS was developed by Wilkins at the MRC Applied Psychology Unit in the 1990s and has been widely used by eye care practitioners since then. It is the only system for treating VS that has been fully described in the scientific literature and that systematically samples human colour space [24]. The system comprises the Pattern Glare Test (PGT) [27], the WRRT [25], Intuitive Overlays (IOs) [9], Intuitive Colorimeter (IC), and PTLs [28]. It is important to note that clinical guidelines are that eye care professionals should carry out a comprehensive eye examination to rule out other causes of any symptoms before IOs or PTLs are prescribed [29].

Both systematic reviews published in 2016 noted that better diagnostic criteria are needed. In response, the following year, Evans et al. published a Delphi study to develop practical diagnostic guidelines for VS [2]. Two rounds of the Delphi process revealed that clinicians were using diagnostic criteria with reasonable consistency and led to diagnostic guidelines based on symptoms and signs, reproduced in Table 1.

**Table 1 Tab1:** Diagnostic indicators of VS from the Delphi study by Evans et al. [2]

At least three of the following six typical symptoms:
1. Words move
2. Words merge
3. Patterns or shadows in text (e.g. “rivers”)
4. Text seems to stand out in 3-D above the page
5. Words or letters fade or darken
6. Discomfort with certain artificial lights and flicker
And
At least two of the following three signs from investigations:
1. Voluntary unprompted use of an overlay for 3 months or more
2. Overlay improves performance at the WRRT by ≥15%
3. PGT result >3 with mid-spatial frequency grating

Below, we present the study protocol for a double-masked randomised controlled crossover clinical trial (RCT). This RCT aims to investigate, in young people aged 9–18 years meeting contemporary diagnostic criteria for VS, whether PTLs prescribed using the IS are beneficial. The overall approach taken in the trial is to maximise the real-world relevance of the study by favouring a pragmatic approach, but not to an extreme extent that would invalidate the scientific rigour of the study.

### Objectives

1a. Assess recollected symptoms experienced during the day with symptom diaries maintained under the two different intervention conditions.1b. Assess immediate symptoms experienced in response to viewing text, with symptom questionnaires presented under the two different intervention conditions.2. Assess academic activity and behaviour by analysing surveys completed by parents/guardians and teachers under the two different intervention conditions.3. Assess reading speed using the WRRT under the two intervention conditions.

## Design and methods

This will be a single-centre, double-masked randomised controlled crossover trial. There will be a 50:50 allocation ratio to evaluate the superiority of a hypothetically optimal intervention over a sub-optimal intervention.

### Study setting

All study testing will be carried out by a state-registered optometrist with extensive experience in this field at the University Eye Clinic, Anglia Ruskin University, [name], UK. This clinic is appropriately equipped for the trial.

### Eligibility criteria

#### Inclusion criteria

To enter the study, participants must meet contemporary diagnostic criteria for VS, as summarised in Table 1. Further eligibility for the study is as follows:Age 9–18 years.Consent (parent/guardian and participant to attend optometric testing and participate in research)Do not anticipate moving from the area in the next 3 months and happy to travel to the Anglia Ruskin University (ARU) eye clinic in Cambridge

In an audit by Evans et al. [30] of 323 participants consulting the first institutional clinic using the IC, the mean age was 14 years. This supports the observation that VS maximally affects secondary school children, who are “reading to learn” rather than “learning to read” [26]. This aligns with the theoretical explanation for VS outlined above: as children progress from large text with widely spaced lines at primary school to smaller more closely spaced text at secondary school, the risk of text possessing the spatial properties that can elicit symptoms increases [31]. It is likely that individuals with significant VS who are untreated will be less likely to continue to university than those without VS [9, 11]. Therefore, there will be a lower prevalence of untreated VS in the university population. It is also likely that the individuals with VS who progress to tertiary education will tend to be those with milder VS. Additionally, there is evidence that the sensitivity to striped stimuli that probably underlies VS on average decreases with age [27]. Therefore, children aged 9–18 years are likely to be a good age for a study of VS. Participants who meet the inclusion criteria will undergo optometric testing (see Supplementary Table 1, Additional file 1) by the lead researcher.

#### Exclusion criteria

Most practitioners who use the IC to prescribe PTLs are optometrists, and the most widely used professional guidance for this profession in the UK is that produced by the College of Optometrists [32]. This guidance recommends that before prescribing coloured filters, a full eye examination is undertaken to exclude other, more conventional, causes of symptoms. The proposed study will follow this advice, applying the clinical exclusion criteria in Supplementary Table 1, Additional file 1. The references in Supplementary Table 1, Additional file 1 are all widely cited clinical publications, and similar criteria are likely used in practice, although the criteria in Supplementary Table 1, Additional file 1 are likely to reflect “best practice”, which will not be followed by all clinicians. If potential participants exhibit any of the conventional optometric anomalies in Additional file 1 and, at least 1 month after that condition has been successfully treated, their symptoms remain and they still meet the diagnostic criteria for VS, then they can be started in the trial.

Further exclusion criteria are as follows:History of wearing PTL.Ocular pathology or systemic pathology that is likely to worsen in the timescale of the study or cause transient blur (e.g. diabetes) or photosensitive epilepsy

### Who will take informed consent?

Participants who are over the age of consent will complete their own signed consent. For participants under the age of consent (16 years old in the UK), their parent/guardian will complete consent, and assent will be obtained from the participant.

### Additional consent provisions for collection and use of participant data and biological specimens

There are no additional consent provisions for the collection and use of participant data. This study does not use biological specimens.

### Explanation for the choice of comparators

The proposed double-masked RCT compares an optimal and sub-optimal colour of PTL to investigate the effectiveness of the IS in reducing the symptoms of VS. The optimal PTL will be detected at the end of the trial, one which creates the least amount of VS symptoms, compared to the sub-optimal PTL which may not reduce VS symptoms to such a great extent.

### Intervention description

The proposed double-masked RCT has five phases (Fig. 1). For a more detailed account of the procedure, please see Additional file 2.Participant recruitment follows three stages (see Additional file 2).Colorimetry, WRRT, and prescribing PTL interventions. Participants will be randomly allocated (with masking) to wear first either optimal (active) colour or sub-optimal (control) colour.Short-term effects of the first pair of PTL:Wilkins Rate of Reading Test (WRRT) at dispensing of first pair (first PTL vs no tint): The test will be administered (following test instruction manual) twice in each condition in the order ABBA with random allocation of PTL or no tint to A or B.Symptoms with the first pair from diaries (see Additional file 5) throughout 1 month of wear and a questionnaire at the end of the month.Academic behaviour survey completed by parents and teachers (see Additional file 6) in the last week of 1 month of wear.After a washout period, each participant will crossover to the other pair, and the researcher will assess the short-term effects of the second pair of PTL, as described in (3) above, including WRRT with second PTL vs no tint in ABBA order.After both pairs have been worn, participants will return for:WRRT with first PTL vs second PTL in ABBA order with random allocation to A or B.The researcher (maintaining masking) will compare symptom diaries from (3) and (4) and WRRT data to decide with the participant about the preferred pair to be dispensed to participants who wish to keep one pair.

**Fig. 1 Fig1:**
[figure not shown]
Participant flow diagram. CYP, children/young persons

### Criteria for discontinuing or modifying allocated interventions

If a participant considers the dispensed spectacle frames are unsuitable or uncomfortable, they can return to the researcher for frame adjustment or dispensing of more appropriate frames. In this scenario, the lens interventions will not be changed.

If a participant experiences aversion or discomfort with one of the interventions, they can stop wearing the PTLs but will be asked to record reasons in the symptom diary. Participants will have previously worn any new optical prescription for 1 month before entering the trial to ensure that there is no non-tolerance to the optical prescription (see Additional file 1).

The participant can remain in the trial, regardless of how much they wear their PTLs, as long as symptom diaries are completed. Written and verbal communication will be provided to participants explaining this when the spectacles are dispensed.

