### Outcomes

#### Primary outcome measures

VS is defined as a condition characterised by symptoms [2], and a previous RCT [5] found symptoms to be the key outcome measure that demonstrated a benefit from individually prescribed PTL [5]. The clinical protocol for the detection, investigation, and management of VS starts with symptoms [26, 33]. Therefore, it is essential for pragmatic research on this topic to concentrate on symptoms. The first primary outcome measure will be symptom assessment using symptom diaries for each intervention. These symptom diaries were used by Wilkins et al. in the original RCT of PTL [5] (see Additional file 5). For the symptom diary, data will be divided into days and hours during which PTLs were worn and symptoms experienced.

The specific measurement variable will be symptom scores representing the number of symptomatic days with pair A vs pair B. The analysis will be carried out at the end of the 3-month trial, as participants will complete diaries throughout the trial.

The second primary outcome measure will be a further assessment of symptoms, measured via symptom questionnaires administered at baseline (before interventions) and at the end of each wearing period (with each intervention). The symptom questionnaire (Figs. 2 and 3) presents participants with questions (A) to (F). At follow-up appointments, the questionnaire wording will be slightly different so that the initial questions assess changes in the originally reported prime symptom (see Additional file 10).

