Initially, all data will be checked by scatter plots of raw data. All data will be tested for normality using the Shapiro-Wilk test, and non-parametric data will be transformed to parametric where possible. Simple comparisons will use paired *t*-tests, or the Wilcoxon signed-rank test as appropriate. For more complex analyses, a Mixed-Effects Model for Repeated Measures (MMRM) will be carried out to account for the crossover design, including fixed effects (intervention type, period, and sequence) and random effects (participant variability).

A confirmatory check will be performed to test for order effects (e.g. whether participants who have the optimal tint after the sub-optimal tint have a statistically different outcome from those who have the sub-optimal tint after the optimal tint). If such an effect is found, key analyses will be repeated whilst controlling for the order effect. In addition, an analysis of the effects of the first tint alone will be compared across participants. The analysis will have low power and will be confirmatory, but it is independent of order effects.

Participants for whom there is a complete set of symptom diary data for at least 2 weeks of wear with both interventions will be analysed on an intention-to-treat basis (ITT) [44]. In the unlikely event that any participants are misallocated, then key analyses will also be run according to a per protocol approach. For the symptom questionnaire conducted before enrolment in the trial and for the academic behaviour surveys, data will only be analysed for participants for whom data are available for *both*interventions [44].

Sensitivity analysis will also be carried out to confirm the robustness of the data produced.

The secondary outcome survey measures will be converted to numeric values. Scores will be aggregated and averaged across surveys and then prepared for statistical analysis using the approaches described above. Tertiary outcome measures will be assessed separately as an exploratory analysis. Tertiary outcome measures will undergo reliability testing using the intraclass correlation coefficient, and analysis for order effects using repeated measures ANOVA, before comparing interventions using standard *t*-tests.

All statistical analyses will be conducted using R (version 4.3.1, R Core Team 2023).

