Another strength of this study is the potential impact on society. If an individual suffers from symptoms of visual distortion, headaches, and eyestrain when reading, there is likely to be a tendency to avoid reading which may impact their educational achievement. This RCT will address the core symptoms of VS and help identify whether PTL have an effect on symptoms and WRRT performance in sufferers of VS using the Intuitive System. Improving the understanding of symptoms and potential treatment in those who report the symptoms of VS can provide health care professionals such as optometrists (who will be the most likely to encounter such symptoms in routine eye examinations) to provide patients with advice and, if appropriate, treatment.

Limitations of the trial are as follows. First, there is a risk with a single-site trial within a specialist clinic that the results may not be directly applicable to a more general population. However, the trial will recruit school-age participants from a variety of schools. Additionally, VS is typically treated in specialist optometric clinics, so the choice to base the trial in such a clinic is pragmatic as it reflects typical clinical practice.

Second, due to the requirement for daily diaries and multiple visits, there is a risk of participant attrition. However, the lead researcher aims to develop a positive rapport with participants and send frequent reminders as explained above. The importance of daily diaries lies within the findings of the original 1994 trial [9], where the daily diary analysis produced findings in the original RCT that were statistically significant, justifying a similar approach in this study. The use of reminders by modern technologies (e.g. SMS, WhatsApp, emails) should improve compliance with diary completion compared with the original study.

The results of this RCT aim to strengthen the evidence base concerning the existence and, if appropriate, treatment of VS using the IS.

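### Staying in the trial is worded as conditional on completing the symptom diary, and the main analysis set is defined by the diary, which puts at risk outcomes that do not need a diary

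*Protocol article*

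**What the plan says.** **Retention.** Under Criteria for discontinuing or modifying allocated interventions: "The participant can remain in the trial, regardless of how much they wear their PTLs, as long as symptom diaries are completed". The next sentence reads: "Written and verbal communication will be provided to participants explaining this when the spectacles are dispensed". Completed is not defined. Under Intervention description, the diary runs through a month of wear for each tint.

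**Diary-based analysis set.** Under Statistical methods for primary and secondary outcomes, participants with "a complete set of symptom diary data for at least 2 weeks of wear with both interventions will be analysed on an intention-to-treat basis".

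**Separate availability rule.** The same section continues: "For the symptom questionnaire conducted before enrolment in the trial and for the academic behaviour surveys, data will only be analysed for participants" who have data for both interventions. No diary condition is attached. The rule does not name the end-of-period questionnaires or the Wilkins Rate of Reading Test (WRRT).

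**The other outcomes.** The second primary outcome is symptoms "measured via symptom questionnaires administered at baseline (before interventions) and at the end of each wearing period (with each intervention"). The school outcome comes from parents or guardians and a teacher (Secondary outcome measures). The WRRT is a timed test given by the researcher (Tertiary outcome measures; Implementation).

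**Recognised risk.** The Discussion says that "due to the requirement for daily diaries and multiple visits, there is a risk of participant attrition".

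**The concern.** The diary is one of five sources of outcome data. The others are the end-of-period questionnaire, the parent survey, the teacher survey and the WRRT, and each can be obtained from a child who keeps no diary. The retention sentence nevertheless makes the diary the condition for staying, and participants are told so. Even if staff never enforce it, a family that has let the diary lapse has been told that the condition for remaining is no longer met.

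The analysis section does not clearly undo this. The only stated set that could cover the end-of-period questionnaire is the diary-defined one, because the separate rule points to a questionnaire completed before any tint was worn.

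Two things are at stake. One is precision on a co-primary outcome and on the secondary and tertiary outcomes. The other is selection: diary-keeping happens after randomisation and may depend on symptoms or on experience with a tint. In a crossover, losing a child during the first period removes that child's whole within-person comparison. The article also justifies two uncorrected primary outcomes on the ground that they are fundamentally different methods. That argument is weaker if having the second depends on completing the first.

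**Working it through.** **1. The passages side by side**

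| Participant | Retention sentence | Analysis section |
|---|---|---|
| Full month of diary, both tints | stays | in the diary set |
| 2 to 4 weeks of diary, both tints | unclear, because completed is undefined | in the diary set |
| No diary, attends every visit | condition not met | surveys usable; end-of-period questionnaire has no clear rule; WRRT has no stated rule |

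The third row is the firm problem, since it does not depend on how completed is defined. The second row is a conflict only if completed means the whole month.

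The availability rule cannot work as written for the questionnaire it names. It asks for data under both interventions from an instrument given before either intervention.

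**2. The plan's own sample size**

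Inputs from Sample size: effect 0.5 within-subject SD, two-sided alpha 0.05, power 90%, 88 needed, 120 recruited.

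- Stated formula: n = 2(1.2816 + 1.9600)² / 0.5² = 84.06, so 85.
- With the t distribution (noncentrality 0.5/√(2/n), n − 2 degrees of freedom), power is 0.8999 at 86, 0.903 at 87 and 0.906 at 88. The smallest n reaching 90% is 87. Rounding up to an even number, or to the block size of 4, gives the stated 88.
- Implied loss allowance: 1 − 88/120 = 26.7%. The article gives no rate.

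**3. Precision of the questionnaire comparison**

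The standard error of the tint difference is proportional to √(2/n). The share of loss due to diaries is not given, so it is taken as an assumption over a range. It counts only people who would otherwise have attended.

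| Share of the 32 allowed losses due to diaries | n as worded | n if decoupled | SE ratio | Power as worded → decoupled |
|---|---|---|---|---|
| None | 88 | 88 | 1.00 | 0.906 → 0.906 |
| Half | 88 | 104 | √(104/88) = 1.09 | 0.906 → 0.946 |
| All | 88 | 120 | √(120/88) = 1.17 | 0.906 → 0.970 |

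Power falls below 90% only when total loss passes about 27%: it is 0.893 at n = 84 (30% loss) and 0.841 at n = 72 (40% loss).

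**4. Selection, as an illustration only**

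Assume about 27% are dropped, with log-odds of dropping that rise by 0.25, 0.5 or 1.0 per within-subject SD of worse symptoms on a tint. Simulation with 400,000 draws and a true difference of about 0.50 gives completer estimates of about 0.50, 0.49 and 0.46. These slopes are assumed; nothing in the article supports a particular value.

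**The case against.** **The sentence is permissive.** It follows a paragraph that lets participants stop wear because of aversion, and its main purpose is to say that not wearing the lenses does not mean leaving. Incomplete diaries are met with SMS reminders. A reader might infer that diary non-completers are withdrawn and do lose their questionnaire, school and reading outcomes. The article does not support that: it states no withdrawal procedure, no timing and no end to data collection. This stands, and the loss is implied rather than shown.

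**Two weeks may be the working meaning of completed.** Reminders are intensive for the first 2 weeks and weekly afterwards, which fits that reading. A reader might infer a direct contradiction between a full month and 2 weeks. It depends on an undefined word. This also stands, but it does not help the child with no diary.

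**The pre-enrolment wording may be a drafting slip** for the end-of-period questionnaires. That is likely, but it leaves a primary outcome without a usable rule until it is corrected.

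**Non-completion might be unrelated to the other outcomes.** The article shows neither that it is related nor that it is unrelated. If unrelated, the cost is precision only; if related, selection is possible. What can be said is that those outcomes do not need the diary to be collected.

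**Attrition may come from burden, and details may sit in the additional files.** The Discussion attributes attrition risk to diaries and visits together, so rewording would not recover everyone. Outcome collection is deferred to Additional file 3. Neither point changes the retention condition that the article itself states and has conveyed to families.

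**Conclusion.** The point holds in a limited form. The article words retention as conditional on an undefined degree of diary completion. It defines its intention-to-treat set by the diary, and it attaches the availability rule to a questionnaire that cannot satisfy it. Following the text would discard obtainable data on a co-primary outcome, the surveys and the WRRT, on a behaviour that arises after randomisation.

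The size is modest. The questionnaire's standard error is between 0% and 17% larger than it need be, and the upper end requires every allowed loss to be a diary non-completer who would otherwise attend. The stated power is not broken within the implied allowance. Selection bias is possible, but its size cannot be derived from the article; under the assumed slopes it is a small attenuation. This is a worthwhile and cheap improvement, not a demonstrated failure of the design.

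**What to change.** **Discontinuation section.** State that participants who have not withdrawn consent remain in follow-up and are invited to all scheduled visits regardless of lens wear or diary completion, and that an incomplete diary affects eligibility only for the diary analysis. Align what families are told at dispensing. This concerns follow-up and data collection only. It leaves untouched the freedom to stop wear or leave, and the use of diaries when the preferred pair is chosen at the end.

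**Statistical methods section.** Limit the 2-week criterion to the diary outcome. Apply the both-interventions availability rule to the end-of-period questionnaires in place of the pre-enrolment one. State that inclusion in the questionnaire, survey and WRRT analyses does not depend on the diary.

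**Cost.** A sentence or two in each section, with no visits or staff beyond those scheduled. The article reports that recruitment has not begun, so the wording can be settled before the first participant is told. The downside is that the two primary outcomes may be analysed on slightly different numbers, which should be reported.
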